### Sample size

The sample size calculation for this trial was performed using the G-Power program (Franz Faul, Universität Kiel, Germany) [45]. We chose an effect size of 0.6 standard deviations described as the lowest among five articles included in a meta-analysis of the effect of exercise studies on sleep apnea [24] as the target for our study. For two groups (training and control) and two assessments (before and after 12 weeks of training), with 90% power and probability of alpha error of 5%, the sample size calculated for analysis of variance with repeated measures would be 16 patients in each group. To compensate for possible participant loss, 40 subjects will be included. Losses after randomization will be included in the intention-to-treat but not in the per-protocol analyses.

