### Statistical methods

Intention-to-treat and per-protocol analyses will be performed for the primary and secondary outcomes. Patients who do not perform the 24 training sessions or who report poor adherence to the healthy lifestyle program during 2 weeks or more will be excluded from the per-protocol analysis. Missing data will be considered as missing, without data imputation.

Means and standard deviation will be used to represent data with a normal distribution and medians and quartiles will be used to describe non-normally distributed data. Natural logarithm transformation will be used before inclusion of non-normally distributed dependent variables in analyses. The significance of the differences between groups, at the baseline, will be tested by the Student *t* test and chi-squared test, for linear and categorical variables, respectively. Generalized estimating equations (GEE) will be used to detect differences between exercise and control groups and time*group interaction. The results with *P* values <0.05 for alpha error will be considered statistically significant. Statistical analyses will be performed using SPSS software (SPSS Inc., Chicago, IL, USA).

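### GEE at P<0.05 with 32 to 40 patients and no stated small-sample correction: under a normal-reference Wald test the true type I error is about 5.7 to 6.7%, not 5%

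*Protocol article*

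**What the plan says.** Under Statistical methods, the group comparison is assigned to one method: "Generalized estimating equations (GEE) will be used to detect differences between exercise and control groups and time*group interaction". The criterion follows: "The results with *P* values <0.05 for alpha error will be considered statistically significant". The software is SPSS. The same section applies intention-to-treat and per-protocol analyses to the primary and secondary outcomes and leaves missing values unimputed. It does not name a working correlation, a covariance estimator, a reference distribution or a small-sample correction.

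Under Sample size, the trial is planned on a different procedure: "the sample size calculated for analysis of variance with repeated measures would be 16 patients in each group", at 90% power and 5% alpha. The inputs are "We chose an effect size of 0.6 standard deviations", two groups and two assessments. The total is then raised: "To compensate for possible participant loss, 40 subjects will be included". Repeated-measures ANOVA does not appear under Statistical methods.

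**The concern.** The usual GEE test divides the estimate by a standard error that is accurate only with many independent patients, then compares the ratio with a normal or chi-square distribution. With 16 to 20 patients per arm, two things go wrong in the same direction. The uncorrected robust variance is too small, here by the factor (n-1)/n. The normal reference also ignores the uncertainty in the estimated variance. The ANOVA F test used for sizing has neither defect when changes are normally distributed.

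The primary outcome and every secondary outcome pass through this test, so the false-positive rate would exceed the declared 5% throughout. The per-protocol set, which excludes patients who do not complete all 24 sessions, can only be smaller, and the excess grows as numbers fall.

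**Working it through.** **Inputs from the protocol article.** Two groups, two assessments, 16 per group after losses, 40 enrolled in equal groups (20 per arm), alpha 0.05, effect size 0.6 SD.

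**Assumptions, not in the document.** Two-sided testing; complete data at both visits; normally distributed changes with equal variance in the arms; a Wald test with a normal (equivalently 1-df chi-square) reference. For the sizing check only: correlation 0.5 between visits, and Cohen's f = 0.6/2 = 0.3.

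**Step 1: the plan's own figure.** For the group-by-time interaction in repeated-measures ANOVA with m = 2 visits, the noncentrality is λ = f²·N·m/(1-ρ). At N = 32, λ = 0.09 × 32 × 2/0.5 = 11.52. The F test on 1 and 30 df has critical value 4.17 and power 0.907. This reproduces 16 per group. At N = 40, λ = 14.4 and power is 0.959. Whether f = 0.3 is the right translation of 0.6 SD for an interaction is a separate question that does not bear on this point.

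**Step 2: what the GEE interaction test is.** With two equal groups of n, two visits and complete data, the GEE interaction estimate is the difference in mean change. The uncorrected robust Wald statistic is

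z = t × √(n/(n-1)),

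where t is the two-sample t statistic on change scores with 2n-2 df. In three simulated data sets, fitted GEE models agreed with this identity (for example, t = 1.4522 and z = 1.4998 at n = 16). The repeated-measures ANOVA F for the interaction is t².

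**Step 3: exact type I error.** Each variant rejects when |t| exceeds a threshold c, so the true error is 2·P(T with 2n-2 df > c):

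- Uncorrected robust SE: c = 1.96 × √((n-1)/n).
- Robust SE with an N/(N-1) variance factor, N = 2n: the c above × √(N/(N-1)).
- Model-based SE with df-corrected scale: c = 1.96.
- ANOVA F or t test: c is the t quantile.

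| Variant | n = 16: c | n = 16: error | n = 20: c | n = 20: error |
|---|---|---|---|---|
| Uncorrected robust | 1.898 | 6.74% | 1.910 | 6.37% |
| Robust × N/(N-1) | 1.928 | 6.34% | 1.935 | 6.05% |
| Model-based | 1.960 | 5.93% | 1.960 | 5.74% |
| ANOVA F / t | 2.042 | 5.00% | 2.024 | 5.00% |

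At 18 per arm the uncorrected robust figure is 6.53%.

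**Step 4: simulation.** The uncorrected robust statistic, computed on change scores in 100,000 runs, rejected in 6.8% (16+16), 6.2% (20+20) and 6.6% (16+20). The pooled t test on the same data stayed at 4.9 to 5.1%. With skewed, untransformed data the robust figures were 6.6% (16+16) and 6.1% (20+20). Full GEE fits, 1,500 runs each with Monte Carlo error of about 0.6 points, gave 7.0% at 16 per arm and 5.8% at 20, consistent with the exact values.

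**Step 5: what it changes in practice.** At 16 per arm, a t statistic on change between 1.90 and 2.04 would be significant by uncorrected GEE but not by the test used for sizing. At 20 per arm the band is 1.91 to 2.02. Any 95% interval built the same way would be 7.1% too short at 16 per arm (1.898/2.042 = 0.929) and 5.6% too short at 20 (1.910/2.024 = 0.944).

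**The case against.** The strongest objection is that the article names GEE and nothing more. The estimator and any small-sample correction are details that an article often leaves to the analysis plan, and GEE with a corrected variance and a t reference would comply with the text as written. This stands as a limit on the size of the finding: no single error rate can be attributed to the trial. A reader might infer that the true level is simply 6.5%, or that P values will certainly be too small. The document does not support that, because the figure depends on an estimator it does not name. What survives is that the section commits the comparison to a large-sample method at this sample size, and every normal-reference variant tried exceeded 5%.

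A reader might also infer that sizing on ANOVA and analyzing by GEE invalidates the sample size. It does not. With two visits and complete data both methods test the difference in mean change with the same estimate; they differ only in the standard-error divisor and the reference distribution.

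The excess is modest, and the section promises P values without mentioning confidence intervals, so the interval figures apply only if intervals are reported. An error rate could be worked out for still fewer completers, but the documents give no completer number below 16 per group.

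**Conclusion.** The concern holds in conditional form. If the GEE test is a Wald test with a normal or chi-square reference and no small-sample correction, its true two-sided type I error lies between about 5.7% and 6.7% for 40 down to 32 patients, an excess of 0.7 to 1.7 percentage points over the declared 5%. The upper end belongs to the uncorrected robust standard error and the lower end to a model-based one. The result rests on complete data at both visits and roughly normal changes, although the simulation with skewed data gave similar values. A small-sample correction set elsewhere would bring the level back close to 5%. The choice of GEE leaves the planned number of patients unaffected. This is a modest defect in the stated analysis, worth correcting because a better-calibrated method is readily available.

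**What to change.** Make the primary analysis a linear model of 12-week AHI (log-transformed if skewed) on group and baseline AHI, tested against the t distribution. Alternatively, use a REML mixed model for the two visits with small-sample degrees of freedom. Apply the same choice to the secondary outcomes.

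If GEE is kept, state the working correlation, a small-sample-corrected variance and a t or F reference, and confirm that the software offers them. The documents name only SPSS and do not show that it provides the corrected estimators.

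The change needs no extra patients, visits or measurements: AHI is already recorded before and after the 12 weeks, and SPSS fits linear and mixed models. The article places all analyses at the end of the study and reports enrollment as ongoing, so as of that document the wording could be changed before results were seen. The price is slightly wider intervals and larger P values than uncorrected GEE would give. The linear model uses only patients with both AHI measurements; the mixed model can also keep those with a baseline value alone.

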**Methods/design:**

This is a randomized clinical trial including patients between 65 and 80 years of age, with obstructive sleep apnea, and an apnea-hypopnea index (AHI) between 20 and 50 events/hour, diagnosed by out-of-center in-home type III polysomnography. Forty subjects will be included and randomly assigned to two equal sized groups. The participants allocated to the intervention group will attend two sessions per week of one-hour strength training for the legs, arms, chest, back, and abdomen and the controls will receive advice on lifestyle change. The primary outcome measure of the study will be the change in apnea-hypopnea index and the secondary outcomes will be the body composition, evaluated by anthropometric and bioelectrical impedance variables; maximum dynamic force, appraised by one-repetition maximum strength test; muscle quality and thickness by ultrasound; physical function assessed by sit-to-stand test, timed up and go test, handgrip strength test. The study duration will be 12 weeks. Intention-to-treat and per-protocol analyses will be performed.

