### Outcomes

#### Primary outcomes

Apnea-hypopnea index (number of apnea and hypopnea events per hour of artifact-free recording in the polygraphy)

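### The plan names two GEE results for AHI at P<0.05 without saying which decides; the group main effect would be the wrong choice, and a baseline-adjusted week-12 comparison is better than either

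*Protocol article*

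**What the plan says.** The Statistical methods section applies intention-to-treat and per-protocol analyses to all outcomes. It then says that generalized estimating equations "will be used to detect differences between exercise and control groups and time*group interaction", and that results with P "values <0.05 for alpha error will be considered statistically significant". No order, split of alpha or deciding test is given.

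Other sections bear on which test is meant:

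- **Abstract, Methods/design:** "The primary outcome measure of the study will be the change in apnea-hypopnea index".
- **Research question:** asks whether training lowers AHI relative to controls, which is a comparison of change.
- **Sample size:** "We chose an effect size of 0.6 standard deviations", applied to a repeated-measures analysis of variance with two groups and two assessments. This gives 16 per group, with 40 to be enrolled in total.
- **Primary outcomes:** AHI, defined only as the "number of apnea and hypopnea events per hour of artifact-free recording in the polygraphy", with neither change nor a time point.
- **Assessment of outcomes:** the sleep recording is made twice, before and after the 12 weeks.

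**The concern.** Two results are listed side by side and only one of them is a clean test of the superiority hypothesis. Because the group difference is listed separately from the interaction, it is natural to read it as the GEE group main effect. With one pre-treatment and one post-treatment measurement, that effect is the average of the baseline difference and the week-12 difference. Training cannot influence the first half.

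Two things are at stake. First, with about 20 per group, a chance imbalance in baseline AHI can push the group term towards or away from significance and be reported as exercise versus control. Second, when the deciding test is not named, the choice can be made after both P values are known.

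**Working it through.** **Inputs.** From the protocol: two groups, two times, 16 per group before losses and 20 per group enrolled, effect 0.6 SD, alpha 5%, power 90%. Not in the protocol and therefore assumed: two-sided tests, pre-post correlation ρ from 0.3 to 0.7, and equal SD (set to 1) before and after unless stated.

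**1. Which test was the trial sized for?** Take f = 0.6/2 = 0.3, m = 2 times and ρ = 0.5.

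- Interaction: λ = N·m·f²/(1−ρ) = 32×2×0.09/0.5 = 11.52. Power is 90.7% at N = 32, so 16 per group is reproduced.
- Between-group effect: λ = N·m·f²/(1+ρ) = 32×2×0.09/1.5 = 3.84. Power is 47.5% at N = 32, and N = 90 would be needed.

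On these inputs the stated size matches the interaction and not the group effect. The match depends on ρ: at f = 0.3 the interaction needs N = 44 for ρ = 0.3 and N = 20 for ρ = 0.7.

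**2. What does the group main effect estimate?** If the baseline difference is 0 in expectation and the week-12 difference is 0.6 SD, the main effect is (0 + 0.6)/2 = 0.3 SD. The three candidate tests, with 20 per group and a t reference, are:

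- Group main effect: difference 0.3, SD √((1+ρ)/2)
- Interaction (difference in change): difference 0.6, SD √(2(1−ρ))
- Week-12 difference adjusted for baseline: difference 0.6, SD √(1−ρ²)

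| ρ | Group main effect: d, power | Interaction: d, power | Baseline-adjusted: d, power |
|---|---|---|---|
| 0.3 | 0.372, 21% | 0.507, 35% | 0.629, 49% |
| 0.5 | 0.346, 19% | 0.600, 46% | 0.693, 57% |
| 0.7 | 0.325, 17% | 0.775, 67% | 0.840, 74% |

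These powers sit well below the 90.7% of step 1 because f = 0.3 in that interaction formula corresponds to a difference in change of 1.2 SD at ρ = 0.5 (16/2 × 1.2² = 11.52). That is a separate matter. Step 1 serves only to identify which test was sized.

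**3. Error rates.** The covariance of the pre/post mean and the change is (Var post − Var pre)/2. It is zero when the variances are equal, so under normality the two tests are then nearly independent.

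- Each test alone, in null simulations of 60,000 runs per setting (16 or 20 per group, ρ 0.3 to 0.8, post/pre SD ratio 1 to 1.5): group effect 4.9–5.2%, interaction 4.7–5.2%.
- Either test counted as success: 1 − 0.95² = 9.75%. Simulated: 9.5–10.0% with equal variances, and 8.8–9.4% with a post SD 1.5 times the pre SD.
- If the group difference instead means the unadjusted week-12 contrast, its correlation with the change contrast is √((1−ρ)/2). The either-test rate is then 8.8–9.4% for ρ 0.3 to 0.7 (normal approximation).

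**The case against.** The strongest defence is that the document already points to one test. The abstract makes change in AHI the primary outcome, the research question compares change, and the sample size reproduces as the interaction. On that reading the nominal error rate stays at 5%. The sentence on GEE can also be taken as a description of what the model examines, with the P<0.05 rule as a general convention. The article does not use the term main effect, and the group difference could mean the week-12 contrast, in which case the averaging argument falls away. Finally, a condensed article may leave the exact contrast to an analysis plan.

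Much of this stands, and it rules out stronger readings. A reader might infer that the plan doubles its type I error rate. It does not say that either result alone is enough, so the 9–10% is conditional on a rule that appears nowhere. A reader might also infer that averaging in the baseline causes the inflation. It does not, because the group test alone holds about 5%; any inflation comes from counting two nearly independent tests as alternatives. Figures of about 11–13% arise with large-sample tests and an uncorrected sandwich variance. The excess over 9.75% is then a small-sample effect, it depends on a variance estimator that the article does not specify, and it does not belong to this point.

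What the defence does not remove is that the analysis section itself names two tests under one threshold and never links the decision to change, while the outcome list drops both change and time point. Nor does it answer the power comparison: data already being collected support a better test than either one named.

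**Conclusion.** The point holds in a limited form. The analysis section leaves the deciding test for AHI open between two named results. Other sections favour the interaction without settling it.

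If the group main effect were used, a true 0.6 SD week-12 effect would be diluted to 0.3 SD, with roughly a one-in-five chance of detection at full enrolment, and chance baseline imbalance would enter the comparison. The baseline-adjusted week-12 difference has the highest power of the three at every correlation examined.

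These figures rest on assumed correlations, equal variances, two-sided tests and 20 analysed per group. Equal variances are uncertain here, because entry restricts baseline AHI to 20–50 events per hour and nothing restricts it at week 12. A false-positive rate of about 9–10% would apply only if either result were accepted as success.

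**What to change.** In Statistical methods, name one primary test: the between-group difference in AHI at week 12, adjusted for baseline AHI. If the GEE with both time points is kept, name the time-by-group interaction instead. State that the group main effect is not used for inference. In Primary outcomes, add the change to week 12 so that the entry agrees with the abstract.

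The cost is a few sentences, with no new data, visits or participants. The article reports enrolment as ongoing at submission and places all analyses at the end of the study, so on that timetable the choice can be fixed before results are seen.

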### Monitoring

Monitoring of the physical activity in the intervention group will be performed by the physical educator after each session in a specific form of the electronic case report form. Patients in the control group will record in a log sheet the number of goals met during each week. The institutional ethics committee will be monitoring the data. All analyses will be performed at the end of the study.

### Study measurements

#### Description of intervention, comparison group, and follow up

The patients will be allocated to strength training or lifestyle advice groups. A detailed description of the phases of the study are shown in Figs. 1 and 2.

**Fig. 1 Fig1:**
[figure not shown]
Standard Protocol Items: Recommendations for Interventional Trials (SPIRIT) figure

**Fig. 2 Fig2:**
[figure not shown]
Flow diagram of the study design

The program will consist of a twice-a-week routine of strength training sessions over 12 weeks. The sessions will be separated by at least 48-hour intervals. Each training session will consist of exercises for the legs, arms, chest, back, and abdomen. The subjects will be instructed to perform the concentric and eccentric phases of each repetition with controlled speed (2–3 seconds at each stage). The training will be divided into cycles of 4 weeks each with intensity and progressive exercise volumes.First cycle: two sets of 12–14 repetitions in the first week using 50% maximal load in order to improve the execution and motor control of exercises, followed by 3 weeks in which individuals will perform three sets of 12–14 repetitions maximum (i.e., performance of sets until concentric failure).Second cycle: three sets of 10–12 repetitions maximum.Third cycle: three sets of 8–10 repetitions maximum.

The rest interval between sets will be 1 to 1.5 minute [46, 47]. The load for each exercise will be adjusted according to the maximal performance of each individual.

The individuals allocated to the control group will receive advice on lifestyle. In addition, individuals will be encouraged to participate in the meetings of an elderly-directed activity group in the primary care unit of the university hospital.

### Ethics

When the subject enters the study, the procedures performed in the physical tests, bio impedance, polysomnography, and training will be explained in detail. The anticipated risks to participants, beyond the occasional pain due to the training effort, will be fatigue and/or dizziness during and/or at the end of exercises. All these signs and symptoms are expected and reversed after cessation of effort. Post-delayed muscle pain, lasting up to 48 hours after the exercise session is a normal effect of strength training, mainly after the first sessions of training. The patient can leave the trial at any time.

The subjects identified with AHI <20 or AHI >50, who are excluded from the study, will be submitted for consultation and treatment in the sleep research clinic in the primary care unit. At the end of the study, all volunteers will be forwarded to the sleep research clinic in the primary care unit for medical treatment.

The trial results will be published in an international journal with impact. The investigators will communicate the trial results to participants via email. No publication restrictions will be implemented.

### Outcomes

#### Primary outcomes

Apnea-hypopnea index (number of apnea and hypopnea events per hour of artifact-free recording in the polygraphy)

#### Secondary outcomes

Muscle strengthMuscle thicknessMuscle qualityBody composition (fluid, fat)Physical function

### Follow up and duration of the study

There will be four visits at the clinical research center for outcome evaluation. Two will be at baseline (a visit to receive the polygraph device and another visit for carrying out evaluation of body composition, physical function, and muscle strength, function, and quality) and two visits at the final follow up (reassessment of the same parameters). The study protocol consists of 12 weeks of strength training twice a week (24 sessions).

### Assessment of outcomes

#### Apnea-hypopnea index

Out-of-center polygraphy will assess the presence and severity of sleep apnea. Portable type III polysomnography monitors (Embletta Gold III, Embla, Broomfield, CO, USA; or SomnoCheck Effort, Weinmann, Hamburg, Germany) will be employed to evaluate: (1) chest effort, (2) abdominal effort, (3) oximetry, (4) nasal airflow, and (5) position, as previously described [48]. Apnea and hypopnea events, respiratory effort related arousals (RERAs), and the apnea-hypopnea and respiratory disturbance index will be reported according to the rules of the American Academy of Sleep Medicine (AASM) [49]. The AHI will define the diagnosis of sleep apnea. Polysomnography will be performed before and after 12 weeks using the same polygraph monitor on both occasions.

